## COST-EFFECTIVENESS EVALUATION

To measure cost-effectiveness of the program, costing analysis will be performed from the societal perspective (both patients/caregivers' and health care providers' perspectives) using an activity-based costing approach. Data on direct costs (e.g. cost of equipment/medication, human resource, transportation, etc) and indirect costs (e.g. loss of income/productivity) of the two interventions will be gathered through interviews with the caregivers and health care providers using a standard costing proforma. Cost-effectiveness of the intervention will then be determined by looking at cost per Quality adjusted life years (QALY) and based on average cost- effectiveness ratio (ACER) and incremental cost-effectiveness ratio (ICER). The Malaysian gross domestic produce (GDP) for the year 2022 will be used in the interpretation of the ACER and ICER data.

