## Alternate Hypothesis

The structured multi-component family-training program is more clinical and cost-effective than usual intervention in improving functional mobility and QoL of persons with PD, carer knowledge, carer QoL and burden among family members of PD when compared to the usual intervention. The family-training program is sustainable and well accepted by family and people with PD.

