## Sampling Method and Sample Size Estimation

Eligible persons with PD will be recruited using a non-probability purposive sampling method. Selected participants (persons with PD) will then be allocated into either the test group (family-training program) or the control group (usual intervention) using simple randomization method. Sample size is calculated using Gpower software version 3.1. This study will use 6x2 Mixed Model Anova with post hoc analysis using Bonferroni. Therefore F-test (ANOVA repeated measures, within-between interactions) is chosen in Gpower software. Study power is set at 95%, alpha set at 0.05 and effect size of 0.41 was chosen based on the effect sizes for the primary outcomes of clinical interest from the study by Bueno et al. (2017). Based on sample size calculation, a total of 18 participants are required. Hence a minimum of nine PD patients and nine family caregivers (n=18 per group) will be recruited in each group which makes it a total of 36 participants in this study. Dropouts are not considered because intention-to-treat analysis will be used and all participants who are enrolled at baseline will be included in the final analysis.

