## Statistical Tools

Statistical Analysis Statistical Package for Social Sciences (SPSS) will be used and variables will be analyzed descriptively, presenting mean and standard deviation. Intention to treat analysis will be performed. Effects of the interventions and comparison between groups will be analyzed using 6 x 2 Mixed Model ANOVA. The level of significance is set at *p*<0.05. Mixed model ANOVA will provide results for main effect of time (before and after therapies), main effect of group (experimental and control group), time and group interaction effect. Statistically significant main effect of time highlights significant changes in the dependent variables following interventions. Statistically significant main effect of group highlights the significant difference between experimental and control groups on the outcomes. Statistically significant time and group interaction effect highlights if experimental group yield the desired effect on dependent

variable significantly compared to control group (Field 2009). Besides aforementioned effects, partial eta squared (ηp²) will also analyzed to display the degree of influence of the independent variable. Cohen (1988) stated that the effect is large for ηp²≥0.14, medium for 0.14>ηp²≥0.06 and small for ηp²≤0.01. Comparison of costs of the two interventions will be done using independent samples *t* test. Statistical tests mapped to objectives in phase III is presented in Table 6.

Table 6 Statistical tests mapped to objectives for phase III

| **Objectives** | **Statistical test** |
| --- | --- |
| To compare the pre and post score of functions, mobility and QOL between persons with PD receiving the structured multi-component family-training program and control group.  To compare the pre and post score knowledge, QOL and burden between family members of persons with PD receiving the structured multi-component family-training  program and control group. | 6x2 Mixed Model ANOVA |
| To evaluate the cost effectiveness of the structured multi-  component family-training program and control group. | Independent sample *t* test |
| To determine the sustainability of the structured multi- component family-training program among the family of  persons with PD. |  |
| - Retention of effect | 6x2 Mixed Model ANOVA |
| - Compliance - Adherence - Drop outs | Descriptive statistics (Mean, standard deviation and percentage) |

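### The ACER is read against GDP on equal terms with the ICER, and the only test mapped to the cost-effectiveness objective compares costs without QALYs

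*Protocol*

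**What the plan says.** The Cost-Effectiveness Evaluation section of the protocol takes a societal perspective, collects direct and indirect costs, and determines cost-effectiveness from cost per QALY, based on the "average cost- effectiveness ratio (ACER) and incremental cost-effectiveness ratio (ICER"). Both ratios have the same benchmark: "The Malaysian gross domestic produce (GDP) for the year 2022 will be used in the interpretation of the ACER and ICER data". The section sets no multiple, does not say per capita, and gives no order of precedence between the ratios.

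Under Statistical Tools, the only method given for the economic data is this: "Comparison of costs of the two interventions will be done using independent samples" *t* test. Table 6 lists that same *t* test, and nothing else, against the objective that begins "To evaluate the cost effectiveness of the structured multi". The general significance level is given as "The level of significance is set at *p*<0.05".

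The claim to be supported is comparative. The Alternate Hypothesis says the programme is "more clinical and cost-effective than usual intervention".

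**The concern.** An ACER divides one arm's cost by all the QALYs that arm accrues, and most of those QALYs would accrue without the programme. It can therefore look favourable whatever the programme adds. The protocol does not treat it as descriptive: it is one of two ratios from which cost-effectiveness is determined, and it is read against the same GDP benchmark as the ICER.

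The mapped test has a related fault. A *t* test of costs contains no health outcome, so neither a significant nor a non-significant result says anything about cost per QALY. Cost-effectiveness is one of the eight specific objectives and part of the hypothesis, yet the analysis assigned to it in Table 6 answers a different question. An analysis plan that followed Table 6 faithfully would carry the mismatch forward.

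**Working it through.** **The plan's own figure.** The economic section states no number. The only related figure is the Phase III sample size: "Study power is set at 95%, alpha set at 0.05 and effect size of 0.41 was chosen" and "Based on sample size calculation, a total of 18 participants are required". Using the noncentral F for a within-between interaction with 2 groups, 3 measurements and a correlation of 0.5 (the last two are my assumptions):

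- noncentrality = f² x N x m / (1 − ρ) = 0.41² x 18 x 3 / 0.5 = 18.2, with 2 and 32 degrees of freedom
- power = 0.962, and 18 is the smallest even N that reaches 0.95.

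So 18 reproduces, giving 9 dyads per arm. This calculation concerns clinical outcomes. The ACER argument does not depend on it.

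**Definitions.** With C for mean cost, Q for mean QALYs, E for programme and U for usual intervention:

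- ACER of the programme = C_E / Q_E
- ICER = (C_E − C_U) / (Q_E − Q_U)
- incremental net monetary benefit at threshold k = k x (Q_E − Q_U) − (C_E − C_U)

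Only the last two contain the comparator.

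**Assumptions, none given in the protocol.** Mean utility is 0.6 to 0.8. The line is 1 x GDP per capita, and costs are in units of GDP per capita. The horizon is 0.5 years if the 6-month visit is counted from baseline, or 12/52 + 0.5 = 0.73 years if it is counted from the end of the 12-week programme.

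**When an ACER passes.** QALYs per arm = utility x horizon, from 0.6 x 0.5 = 0.30 to 0.8 x 0.73 = 0.58. An arm is below the 1 x line whenever its cost is under 0.30 to 0.58 GDP per capita, whatever the other arm does. At 3 x GDP per capita the ceiling triples, to about 0.90 to 1.75.

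**Illustration.** Assumed costs are 0.2 (programme) and 0.1 (usual intervention), so the extra cost is 0.1.

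| Incremental QALYs | Programme ACER | ICER | Net benefit at 1 x |
| --- | --- | --- | --- |
| 0 | 0.2/0.585 to 0.2/0.30 = 0.34 to 0.67 | undefined | 0 − 0.1 = −0.10 |
| −0.01 | 0.2/0.575 to 0.2/0.29 = 0.35 to 0.69 | dominated (0.1/−0.01 = −10) | −0.01 − 0.1 = −0.11 |
| +0.01 | 0.2/0.595 to 0.2/0.31 = 0.34 to 0.65 | 0.1/0.01 = 10 | 0.01 − 0.1 = −0.09 |

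The ACER passes in all three rows and the incremental result fails in all three. In the second row the raw ratio of −10 is numerically below the line, so the signs of its two parts must be read. Net benefit avoids that trap.

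**The cost *t* test.** By the noncentral *t*, two-sided 0.05 (sidedness is not stated), 9 per arm gives 17% power at a standardised difference of 0.5 and 36% at 0.8. A difference of 1.41 is needed for 80%. If all 18 people per arm were treated as independent, the figures would be 31%, 65% and 0.96. A non-significant result is weak evidence of equal cost, and even a precise one would not address QALYs.

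**Precision of incremental QALYs at 9 per arm.** Half-width of the 95% interval = 2.12 x SD x √(2/9). For an assumed SD of 0.05, 0.10 or 0.15 this is 0.05, 0.10 or 0.15 QALY.

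**The case against.** The strongest reply is that the ICER is already planned. With no gain it is undefined, and with a loss the programme is dominated, so the failure would be visible in a promised output. EQ-5D is also compared between groups by the mixed ANOVA. This stands. A reader might infer that cost-effectiveness rests on the ACER and the cost *t* test alone, or that a programme without benefit must be declared cost-effective. The text supports neither.

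A reader might also infer that both arms could satisfy the hypothesis together. They cannot. Both ACERs can lie below the line, but the hypothesis is comparative. In the zero-gain case the programme's ACER is twice that of usual intervention (0.67 against 0.33 at 0.30 QALY), so setting the two averages side by side would count against the programme. That comparison is still no substitute for the incremental one. For a positive QALY gain, the programme's ACER exceeds the other arm's exactly when the ICER exceeds C_U/Q_U, so the ranking uses usual care's own average as the threshold and not GDP.

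The *t* test can be defended as a comparison of arithmetic mean costs, which is the right quantity for costs, and the text describes it that way. The fault lies in Table 6, which assigns it as the sole method for the whole objective.

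Finally, the protocol's silence on ICER uncertainty and on adjustment for baseline utility is not an error, since an analysis plan not shown may cover both. Imprecision at 9 per arm comes from the sample size, and no choice of economic analysis removes it.

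**Conclusion.** The point holds in a limited form. The protocol makes the ACER a criterion equal to the ICER against an unspecified GDP threshold, with no rule for disagreement, and an ACER below that threshold is compatible with zero or negative incremental QALYs. Table 6 maps a comparative cost-effectiveness objective to a test containing no QALYs, so the mapped test cannot support the hypothesis. A wrong conclusion is possible under the wording but not built in, because the ICER would expose a lack of benefit if it is given precedence.

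The ceiling of 0.30 to 0.58 GDP per capita rests on the assumed utilities, horizon and 1 x line. The protocol gives no costs, so whether the arms fall under it is unknown. That the ACER leaves out the comparator, and the *t* test leaves out QALYs, depends on none of these assumptions.

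**What to change.** In Cost-Effectiveness Evaluation, state that the incremental result decides: either the ICER, with the signs of both increments reported, or incremental net monetary benefit at a stated multiple of 2022 GDP per capita. Say that the ACER is descriptive only.

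In Table 6, map the objective to a joint analysis of incremental cost and incremental QALYs with an interval. One option is a bootstrap that resamples dyads, with QALYs from EQ-5D at week 0, week 12 and the 6-month visit, adjusted for the baseline EQ-5D already collected. Say whether the horizon runs from baseline or from programme completion. Keep the *t* test only to describe costs.

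This costs protocol wording and some analysis work, and uses cost and EQ-5D data already planned. The drawback is that the result will show wide uncertainty at 9 dyads per arm, where a bootstrap is itself fragile.

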## ASSESSMENT OF PROGRAM SUSTAINABILITY

Program sustainability will be assessed by measuring all participants’ (persons with PD and their family caregiver) outcomes again at a 6-month follow-up and comparing the participants' variables with previously measured data. The aim is to determine if the positive effects of the training program can be maintained at least for 6 months of the program completion. Sustainability also will be measured based on compliance to exercise, adherence to the module component and dropout rate.

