## HYPOTHESIS

- 1. **Null Hypothesis**

The structured multi-component family-training program is not more effective clinically and by cost, when compared with a usual intervention in improving functions, functional mobility and QoL of persons with PD, carer knowledge, carer QoL and burden among family members of PD when compared to the usual intervention. The family-training program is not sustainable and not well accepted by family and people with PD.

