## (C) Measurement of outcomes

Outcomes will be evaluated at week 0, 12 and at 6-month follow up. Program sustainability will be assessed at a 6-month follow up by a blinded assessor**.** Summary of the study procedure is as attached in the Figure 6.

Will be excluded based on

exclusion criteria

Persons with PD and their family caregivers will be screened in medical rehabilitation department of UKMMC (n=36)

Eligible participants will be randomized based on simple random sampling (n=36) and baseline measurements will be taken

Assessment after 12th week (n=36, intention to treat approach)

Allocated to control group; usual intervention (n=18)

Allocated to experimental group; family caregiver- training program (n=18)

[figure not shown]

[figure not shown]

[figure not shown]

[figure not shown]

Results compilation and reporting

Sustainability assessment of outcomes after 6 months

1. Sustainability of effects based on clinical effects measured at week 12
2. Adherence, compliance, drop outs and adverse events.

Assessment of outcomes after 12th week

Functions and mobility measured using MDS-UPDRS and TUG respectively

QoL of patient and family caregivers measured using EQ-5D.

Caregiving burden measured using Zarith Burden Interview.

Knowledge of carer measured using adapted , translated and validated questionnaire

Figure 6 Flow Chart of Phase III

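### The test assigned to retention of effect, the three-visit time-by-group interaction, has the same power whether the week-12 benefit is fully kept or fully lost at 6 months

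*Protocol*

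**What the plan says.** All references are to the protocol.

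- **Visits.** Measurement of outcomes (Phase III): "Outcomes will be evaluated at week 0, 12 and at 6-month follow up".
- **Aim.** Assessment of Program Sustainability: "The aim is to determine if the positive effects of the training program can be maintained at least for 6 months". The method given there is "comparing the participants' variables with previously measured data". No visit pair, between-arm contrast or retention criterion is stated.
- **Test.** Table 6 lists "Retention of effect | 6x2 Mixed Model ANOVA". Objectives 5 and 6 (efficacy) have the same test.
- **How it is read.** Statistical Tools takes three effects from the ANOVA: time, and "main effect of group (experimental and control group), time and group interaction effect". A significant interaction is read as the experimental arm achieving the desired effect relative to control.
- **Sizing.** Phase III Sampling Method and Sample Size Estimation uses the G*Power within-between interaction F-test with effect size 0.41, alpha 0.05 and power 95%. It arrives at 18, which is 9 patients and 9 caregivers per arm. It also mentions Bonferroni post hoc analysis without naming the comparisons. Neither Statistical Tools nor Table 6 repeats this.
- **Hypotheses.** Sustainability forms part of the null: "The family-training program is not sustainable and not well accepted by family and people with PD". The alternative asserts the opposite.

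**The concern.** Retention is a question about one visit: is the programme arm still ahead of control at 6 months? The omnibus interaction asks something else, namely whether the between-arm difference varies at all across the three visits. A benefit that appears at week 12 and disappears by 6 months varies across visits just as a lasting benefit does. If the interaction is reported in the retention row of Table 6, a programme whose effect has gone can show the same significant result as one whose effect has lasted. Sustainability is objective 8 and is written into both hypotheses, so this would bear on a headline conclusion.

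**Working it through.** **Inputs.** From the protocol: 2 arms, 9 per arm for each participant type, 3 visits, f = 0.41, alpha 0.05. Assumed, because the protocol does not give them: correlation ρ = 0.5 between any two visits, sphericity, and a control arm that does not change. Effects are in units of the SD between persons at one visit.

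**1. The plan's own figure.** For the within-between interaction, λ = f²·N·m/(1−ρ), with df (m−1) and (N−2)(m−1). With N = 18 and m = 3:

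λ = 0.41² × 18 × 3 / 0.5 = 18.15, df 2 and 32, power 0.962.

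The smallest N reaching 95% is 17, or 18 for equal arms, so the stated 18 is reproduced. At ρ = 0.5, m = 2 gives 22 and m = 6 gives 12. The 6x2 label does not itself show three visits; that number comes from the visit schedule, and the sample size agrees with it.

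**2. Kept against lost.** Let δ be the between-arm difference at the three visits. The interaction noncentrality is λ = (n/2)·Σ(δₜ − mean δ)²/(1−ρ).

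- Fully kept, δ = (0, D, D): mean 2D/3, sum of squares 4D²/9 + D²/9 + D²/9 = (2/3)D².
- Fully lost, δ = (0, D, 0): mean D/3, sum of squares D²/9 + 4D²/9 + D²/9 = (2/3)D².
- Half kept, δ = (0, D, D/2): mean D/2, sum of squares D²/4 + D²/4 = D²/2.

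With n = 9 and ρ = 0.5, λ = 9 × sum of squares, so kept and lost both give 6D². The planned λ of 18.15 corresponds to D = √(18.15/6) = 1.74 SD.

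| Interaction power | Kept | Lost | Half kept |
|---|---|---|---|
| D = 1 SD (λ = 6, 6, 4.5) | 0.54 | 0.54 | 0.42 |
| D = 1.74 SD (λ = 18.15, 18.15, 13.6) | 0.96 | 0.96 | 0.89 |

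Simulation at D = 1 SD (20,000 trials per pattern) gave 0.540 kept and 0.537 lost, with mean partial eta squared 0.194 and 0.193. A half-kept effect is less likely to be significant than a wholly lost one.

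**3. Dependence on the correlation pattern.** Exact equality needs equal correlations. With first-order autoregressive correlation of 0.5 and D = 1 SD, the multivariate noncentrality is 4.8 kept and 7.2 lost, so a lost effect is then easier to declare significant.

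**4. The other effects, at D = 1.74 SD.**

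- Time: with a flat control arm, identical for kept and lost, as for the interaction.
- Group: λ = (n/2)(mean δ)²/((1+2ρ)/3), df 1 and 16. Kept 4.5 × 1.16²/0.667 = 9.1, power 0.81. Lost 4.5 × 0.58²/0.667 = 2.3, power 0.29. It differs, but it averages all visits, baseline included.
- Between-arm test at 6 months at alpha/3, λ = (n/2)δ₃²: 0.83 kept, 0.017 lost.
- Week 12 against 6 months within the programme arm at alpha/3, λ = n × loss²/(2(1−ρ)): rejects 0.017 kept, 0.97 lost.

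**5. A contrast that isolates 6 months.** Between-arm difference in change from week 0 to 6 months, λ = (n/2)δ₃²/(2(1−ρ)), df 1 and 16, two-sided 0.05. At D = 1.74 SD the power is 0.93 kept, 0.41 half kept and 0.05 lost.

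**6. Within-arm loss read by significance.** Paired t, n = 9, SD of change 1 SD (which ρ = 0.5 implies).

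| True loss | Power at 0.05 | Power at alpha/3 |
|---|---|---|
| 0.5 SD | 0.26 | 0.13 |
| 1 SD | 0.75 | 0.53 |
| 1.64 SD | 0.99 | 0.94 |

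**The case against.** The strongest reply is that the plan contains more than the interaction. The group main effect does respond to a lost benefit (0.81 against 0.29), descriptive means and SDs would show one, and Bonferroni post hoc tests are planned. If those tests include the 6-month comparisons, they separate the patterns sharply. Choosing contrasts is also often left to a statistical analysis plan, which may exist. This stands in part: a reader might infer that the whole ANOVA gives one answer in both cases, and that is not so. The equality holds for the interaction, and for time when controls are flat. But the group effect does not isolate 6 months, and the post hoc comparisons are neither named nor carried into Table 6. The protocol did not leave the matter open either, since it assigned a specific test to retention.

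Three further inferences go beyond the documents:

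- **That objective 8 as a whole cannot be answered.** Compliance, adherence and dropout are assessed descriptively and are unaffected.
- **That a non-significant loss is nearly assured with 9 per arm.** A full loss of 1.64 SD would be detected with power 0.99, or 0.94 at alpha/3. The weakness concerns modest losses.
- **That the protocol defines maintained as no significant loss.** It states no such rule; it states no rule at all.

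**Conclusion.** The concern holds for the retention-of-effect row of Table 6. The interaction that the trial is sized on, and that the protocol reads as benefit, has equal power for a fully kept and a fully lost 6-month effect: 0.54 at 1 SD and 0.96 at the planned effect size, with 9 per arm. This rests on three visits and equal correlations. The value 0.5 sets the power figures, but the equality holds for any common correlation; under autoregressive correlation the interaction favours the lost pattern. The post hoc tests could rescue the analysis, but as written nothing says which comparison answers the aim. The protocol should be changed on this point, though the rest of the sustainability assessment is not in doubt.

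**What to change.** In Assessment of Program Sustainability, Statistical Tools and Table 6, replace the omnibus ANOVA in the retention row with:

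1. The between-arm difference at 6 months, adjusted for the baseline value, with 95% CI. Claim sustained benefit only if the interval excludes zero in favour of the programme.
2. The change from week 12 to 6 months in the programme arm, with 95% CI, and a statement that a non-significant loss is not evidence of retention.

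A prespecified margin for acceptable loss could be added but is not essential. With n = 9 and SD of change 1 SD, the half-width of the 95% CI is about 2.306 × 1/√9 = 0.77 SD, so even an observed loss of zero would fail any margin smaller than that.

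The cost is wording only, with the same visits and data. The downside is that a sustained-benefit claim becomes harder to make: on the change contrast in step 5 of the working, a half-kept effect at the planned size would reach significance with power of only 0.41.
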